### Interventions

The patients allocated to the intervention group will participate in an aerobic training protocol on a cycle ergometer during the period in which they are hospitalized and undergoing the chemotherapy cycle. The training will be carried out with daily sessions for 4 days lasting 40 minutes as long as the chemotherapy cycle continues. Exercise on the cycle ergometer will begin with a 5-minute warm-up and will progress to 30 minutes of exercise at a speed corresponding to 40%-60% of the heart rate reserve calculated by the Karvonen formula [30]: (220 – age) – (heart rate of rest × % intensity) + resting heart rate. The exercise will end with 5 minutes of recovery. The objective will be to maintain the patient at a score of 12 for the perception of dyspnea and physical fatigue, as measured by the Borg scale [31] (12 indicates that the patient’s dyspnea and physical fatigue is above “relatively easy” and below “slightly tiring”), during exercise on the cycle ergometer. The Borg scale presents a range of scores from 6 (no effort) to 20 (maximum effort). Therefore, if the patient is considered fit by the physiotherapist, the speed on the cycle ergometer will be gradually increased until the patient reaches 60% of the heart rate reserve. We will record heart rate and peripheral oxygen saturation (Palmsat 2500 pulse oximeter; Nonin), dyspnea and physical fatigue (Borg scale) [28], and blood pressure (Premium Aneroid Sphygmomanometer and Littmann Classic II Stethoscope) before, during, and after each physical training protocol session. The session may be interrupted at any time if the patient presents signs or symptoms such as dizziness, dyspnea, fatigue, or nausea. If the patient requires any emergency assistance during the period in which they are undergoing physical training supervised by the study physiotherapist, the same physiotherapist will contact the medical team on duty responsible for the patient in the oncology ward to provide the necessary assistance to stabilize the condition of the patient. To assist in blinding the evaluator, a booklet titled “Why do I need to move when I am hospitalized” [32] will be given to patients in both groups. The cycle ergometer will always be removed from the patient’s room after the training session to ensure blind evaluation.

The patients allocated in the control group will receive the same booklet (“Why do I need to move when I’m hospitalized”), which uses illustrations and short texts to encourage patients to spend more time in their chair, walk, and go up and down stairs (with a companion) [32]. This booklet will be delivered and explained by a trained physiotherapist and the participant will keep it for any questions and consultations.

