## Abstract

**Background:**

One strategy to prevent adverse effects resulting from chemotherapy treatment is to perform physical exercises during treatment. However, there is still no consensus on the best type and intensity of exercise, nor when it should be started. Most studies have been carried out in patients with breast cancer, usually a few weeks after starting chemotherapy, on an outpatient basis 2 to 3 times a week. The main differences in our study are that we carried out physical training in hospitalized patients undergoing a cycle of chemotherapy for cancer treatment and that this training was carried out 5 times a week and was not restricted to a specific type of cancer.

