## Introduction

Cancer is already the biggest public health problem in the world. In Brazil, the estimate for the 2023-2025 period is that there will be 704,000 new cases of cancer per year (excluding cases of nonmelanoma skin cancer) [1]. One of the main forms of treatment for cancer is chemotherapy, which consists of a systemic treatment in which a drug is used to interfere with cell proliferation, targeting its DNA or RNA and its metabolism [2]. The costs of cancer treatment in the United States already reach US $158 billion per year [3], and in Brazil, they exceed R $3.5 billion (US $700 million) [4]. The application of these resources requires health care staff, medications used directly and indirectly in treatment, equipment, and hospitalization days.

Treatment with chemotherapy involves a series of side effects, including nausea, vomiting, diarrhea, and febrile neutropenia, which are treated with supplementary medications. These adverse effects have a major impact on patients’ lives, as well as on adherence and compliance with the recommended dose of treatment, and they are also associated with an increase in the rate of hospitalization. At least one-third of women undergoing adjuvant chemotherapy treatment for breast cancer are unable to complete the prescribed dose of treatment due to adverse effects, thus compromising the prognosis of the disease [5].

Physical exercise in patients with cancer during chemotherapy has been tested in randomized trials [5-11] and appears to improve physical function, fatigue, symptom burden, and the quality of life of patients, in addition to allowing the nonreduction of chemotherapy doses. However, most studies have been carried out on an outpatient basis, involved patients with breast cancer, used 3 weekly exercise sessions, and evaluated fatigue as the primary outcome. There are still no clinical trials testing the effect of exercise in a hospital environment with daily sessions (Monday to Friday) carried out during the chemotherapy cycle.

Therefore, our objective is to evaluate the effects of aerobic training on chemotherapy-related symptoms (nausea, vomiting, asthenia, and sensation of weakness), fatigue, mobility, clinical complications, and length of hospital stay in patients during the drug treatment cycle. Furthermore, we also aim to evaluate the adverse effects of aerobic training, patient satisfaction with the proposed intervention, its implementation, and its cost-effectiveness.

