### Procedures

During the protocol period, all patients admitted to the oncology ward who are identified and meet the eligibility criteria will be invited to participate in the study by the evaluating physiotherapist. These eligible patients will be informed about the objectives of the study and invited to sign the informed consent form. Next, the patients will be evaluated regarding anthropometric and clinical characteristics, fatigue, and mobility, as well as the occurrence, frequency, intensity, and discomfort of the main adverse effects of chemotherapy. After the initial assessment, patients will be randomized into an intervention group, which will perform aerobic exercise sessions, and a control group, which will receive a booklet with guidelines (the same booklet will be given to the patients in the intervention group). The next day, the intervention will begin. Aerobic training will be carried out from Monday to Friday while the patients are hospitalized for the chemotherapy cycle in the oncology ward. Before carrying out the day’s aerobic exercise session, the patients will be asked if they feel any type of discomfort that is related to the previous day’s training (for example, muscle or joint pain in the lower limbs). If for any reason chemotherapy is interrupted for a patient, the exercises will also be interrupted, and as soon as chemotherapy treatment is resumed, the exercise will also be resumed. The booklet will be given to the patients and explained by a trained physiotherapist. Patients will be re-evaluated on the day following the last day of the chemotherapy cycle regarding the occurrence, frequency, intensity, and discomfort of adverse effects of the treatment, as well as fatigue, mobility, and satisfaction with the proposed intervention.

After the study intervention period, patients who need it will receive routine physiotherapeutic care provided by the physiotherapy team at the hospital. The incidence of clinical complications from chemotherapy and the length of hospital stay will be assessed as outcomes until hospital discharge. All data will be collected by a blinded assessor. Additionally, data will be coded and entered into a Microsoft Excel spreadsheet and will be double-checked before analysis. A visual representation of the study design is presented in Figure 1.

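### The planned number of exercise sessions is stated in incompatible ways: 4 days in Interventions, but Monday to Friday or five times a week elsewhere

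*Protocol article*

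**What the plan says.** Four places in the protocol article describe how often patients train.

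- **Methods, Interventions:** "The training will be carried out with daily sessions for 4 days lasting 40 minutes as long as the chemotherapy cycle continues".
- **Methods, Procedures:** "Aerobic training will be carried out from Monday to Friday while the patients are hospitalized for the chemotherapy cycle in the oncology ward".
- **Abstract, Background:** "this training was carried out 5 times a week". This is listed as one of the study's main differences, together with the inpatient setting and the absence of a restriction to one cancer type.
- **Introduction:** the gap in the evidence is described as the lack of trials of exercise "in a hospital environment with daily sessions (Monday to Friday) carried out during the chemotherapy cycle".

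Two rules in Procedures also affect how many sessions a patient can have. Training starts the day after baseline assessment and randomization ("The next day, the intervention will begin"), and "If for any reason chemotherapy is interrupted for a patient, the exercises will also be interrupted", to be resumed when chemotherapy resumes.

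The article gives no cycle length, no total number of sessions, and no rule linking the 4 days to the weekday schedule.

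**The concern.** The Interventions sentence sets a fixed number of days and, in the same breath, an open-ended duration. The two agree only if the cycle happens to offer exactly that many training days. The other three places give a weekday schedule with no cap. A physiotherapist working from Interventions could stop after the fourth session, while one working from Procedures would continue to the end of the cycle.

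Three planned quantities draw on the session count:

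- the adherence rate, reported descriptively (Statistical Design);
- the per-protocol sensitivity analysis of the economic evaluation (Statistical Design);
- the intervention cost, which is built partly from physiotherapy sessions at reference fees (Assessments), if planned rather than delivered sessions are costed.

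The article also offers training frequency as one of the features that set this trial apart from earlier ones. A reader of the results would need to know which frequency was planned.

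**Working it through.** **Inputs from the article.** Session length is 40 minutes, which agrees with its parts: 5 min warm-up + 30 min exercise + 5 min recovery = 40 min. The two schedules are 4 days (Interventions) and each Monday-to-Friday day in the cycle (Procedures, Abstract, Introduction).

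**Assumed input.** The article gives no cycle length, so the length of the training window (days available from the first session) is varied below.

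**One full week, five weekdays available.**

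- Interventions: 4 × 40 = 160 min, of which 4 × 30 = 120 min is the main exercise phase.
- Weekday schedule: 5 × 40 = 200 min, of which 5 × 30 = 150 min is the main exercise phase.
- Ratio: 160 / 200 = 0.80, that is, 20% less.

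**Planned sessions by assumed window, reading the 4 days as a total.** The weekday count is the number of Monday-to-Friday days in the window, over all possible start days.

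| Window (assumed) | 4-day total | Weekday schedule |
|---|---|---|
| 5 days | 4 | 3 to 5, by start day |
| 7 days | 4 | 5 |
| 10 days | 4 | 6 to 8, by start day |
| 14 days | 4 | 10 |

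In the 5-day row, a Tuesday start gives 4 on both readings. A Wednesday start gives 3 weekdays against 4 calendar days, so the sign of the gap there depends on whether weekend days count towards the 4. From 7 days upward every window holds at least five weekdays, so that question no longer matters.

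**If the 4 days are read per week instead.** Over 14 days the comparison is 2 × 4 = 8 against 2 × 5 = 10, again a ratio of 0.80. The article does not say that the 4 days are per week.

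**Effect on adherence for a patient who completes 4 sessions.**

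- Denominator 4: 4/4 = 100%.
- Denominator 5 (full week): 4/5 = 80%.
- Denominator 10 (14 days, 4 days as a total): 4/10 = 40%.

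**The case against.** The best case for the plan is that only one phrase is out of line. Mode, session length, heart-rate range and Borg target are all fixed. Interventions and Procedures agree that training lasts as long as the in-hospital cycle, and Procedures adds a rule for interruption and resumption. The 4 days clash even with the rest of their own sentence, which may point to loose wording rather than a rival schedule. There is also an innocent explanation: a patient assessed on the Monday of a Monday-to-Friday cycle starts on Tuesday and has four sessions under either text.

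Much of this stands, and it limits the point in four ways.

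- A reader might infer that the tested dose as a whole is undefined. It is not; the conflict concerns only the number and frequency of sessions.
- A reader might infer that the texts differ for every cycle with more than four weekdays. The next-day start shows otherwise.
- A reader might infer that the missing definitions of adherence and of the per-protocol set are faults in themselves. They may sit in an analysis plan or full protocol that is not shown.
- A reader might infer that the costed sessions must differ by 20%. The article does not say whether planned or delivered sessions are costed; if delivered, realised cost does not depend on the wording.

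The innocent explanation does not remove the contradiction. The article never offers it, it fits one assessment day and a cycle of about a week, and it does not square with a stated five sessions a week. Nor is this a detail left to a fuller document: the article states the frequency itself, in ways that cannot all hold.

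**Conclusion.** The point holds as an inconsistency in the stated number of sessions. Its size cannot be fixed from the article because cycle length is missing. Under the assumptions shown, it runs from no difference in some short windows, through 4 versus 5 sessions in a full week, to 4 versus 10 in 14 days. The 20% figure rests on five available weekdays, and the 14-day contrast on reading the 4 days as a total.

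The consequences are secondary but real: adherence, a per-protocol set, and planned intervention cost all depend on the count. The effectiveness comparison follows intention to treat and can be computed under either text, so the contradiction does not invalidate it. What it leaves unclear is which planned regimen that comparison evaluates. The correction is worth making, particularly because the Results section says recruitment is ongoing.

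**What to change.** Reconcile the Interventions section with the Abstract, Introduction and Procedures so that one schedule is stated everywhere, and say how it applies given the next-day start and the interruption rule. Which schedule is right is for the investigators to state. Use the reconciled schedule as the basis for the adherence rate and for the per-protocol set, wherever those are formally defined, and say whether intervention cost uses planned or delivered sessions.

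Report the number of sessions actually delivered to each patient, including those already treated, so that readers can see the regimen received whichever text was followed.

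The cost is a change of wording. Interventions provides for heart rate, oxygen saturation, Borg scores and blood pressure to be recorded at each session, so delivered sessions should be countable from those records. That is an inference, since the article does not mention a session log. Making the change before the analysis settles the planned count before results are seen.

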## Results

In March 2023, the clinical trial registration was approved. Recruitment and data collection for the trial is ongoing, and the results of this study are likely to be published in late 2025.

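### The printed heart-rate formula for the training cannot give 40%-60% of heart rate reserve: it returns targets above 220 − age that fall as intensity rises

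*Protocol article*

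**What the plan says.** All the relevant text on intensity is in the Interventions section of the Protocol article. The main block of each session is "30 minutes of exercise at a speed corresponding to 40%-60% of the heart rate reserve calculated by the Karvonen formula". The formula follows in the same sentence; after its opening bracket it reads "220 – age) – (heart rate of rest × % intensity) + resting heart rate". Progression is described in the same terms: for a patient judged fit, "the speed on the cycle ergometer will be gradually increased until the patient reaches 60% of the heart rate reserve".

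The section also gives a target for perceived effort, on a Borg scale from 6 to 20: "The objective will be to maintain the patient at a score of 12 for the perception of dyspnea and physical fatigue". It provides for stopping: "The session may be interrupted at any time if the patient presents signs or symptoms", with dizziness, dyspnea, fatigue and nausea as examples. It lists what is measured before, during and after each session: "We will record heart rate and peripheral oxygen saturation", together with Borg scores and blood pressure. No other heart-rate calculation appears in the article.

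**The concern.** Heart rate reserve is the gap between maximum and resting rate, here (220 − age) minus the resting rate. A target at a given share of reserve adds that share of the gap to the resting rate. It must therefore lie between the resting rate and 220 − age, and must rise with the percentage. The printed brackets tie the percentage to the resting rate alone, so the result has neither property.

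Aerobic training is the intervention under test, and this line is the one place where its stated intensity is turned into a number of beats per minute. Anyone who copies it to deliver or replicate the training gets a wrong target. The participants are inpatients receiving chemotherapy, so a target of that kind would be a safety matter if it were ever used. The article does not show that it has been.

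**Working it through.** **Inputs.** The formula, the 40%-60% range and the 60% progression limit come from the Interventions section. The article gives no ages or resting rates for worked cases, so those below are assumptions chosen to span a wide range.

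Let M = 220 − age, R = resting heart rate and p = intensity as a fraction.

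**Algebra.**

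- Printed: M − (R × p) + R = M + R(1 − p).
- Stated share of reserve: (M − R) × p + R.
- Printed minus stated: M + R − Rp − Mp + Rp − R = M(1 − p).

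For any p below 1 and any positive R, the printed value exceeds M by R(1 − p), which is 0.6R at 40% and 0.4R at 60%. Its slope in p is −R, so the 60% target is lower than the 40% target. Expressed as a share of reserve it is 1 + R(1 − p)/(M − R), which is always above 100%. None of this depends on the assumed patients.

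**Reproducing the stated 40%-60%.** First case, age 50 and R = 70, so M = 170 and the reserve is 100:

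- Printed: 170 − 28 + 70 = 212 at 40%; 170 − 42 + 70 = 198 at 60%.
- Stated: 100 × 0.4 + 70 = 110; 100 × 0.6 + 70 = 130.
- Share of reserve actually given by the printed line: (212 − 70)/100 = 142% and (198 − 70)/100 = 128%.

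The stated range is not reproduced. The same steps for three more cases (bpm):

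| Age, R (assumed) | 220 − age | Printed, 40% / 60% | Stated, 40% / 60% | Excess, 40% / 60% |
|---|---|---|---|---|
| 30, 60 | 190 | 226 / 214 | 112 / 138 | 114 / 76 |
| 50, 70 | 170 | 212 / 198 | 110 / 130 | 102 / 68 |
| 65, 75 | 155 | 200 / 185 | 107 / 123 | 93 / 62 |
| 80, 90 | 140 | 194 / 176 | 110 / 120 | 84 / 56 |

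A separate grid of ages 30, 45, 60 and 75 with resting rates of 60, 75 and 90 puts the printed line at 118% to 198% of reserve for intensities of 40% to 60%. In all 12 combinations the value is above 220 − age and lower at 60% than at 40%.

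**Other readings of the printed line** (age 60, R = 75, M = 160):

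- Percentage entered as a whole number: 160 − 75 × 40 + 75 = −2765; 160 − 75 × 60 + 75 = −4265.
- Second bracket closed after the last term: 160 − (30 + 75) = 55; 160 − (45 + 75) = 40, both below the resting rate.
- Second pair of brackets dropped: no change, because multiplication takes precedence.

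Moving the bracket so that the percentage multiplies (M − R) gives 85 × 0.4 + 75 = 109 and 85 × 0.6 + 75 = 126, which are 40% and 60% of reserve by construction.

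**The case against.** The best defence is that this is a slip of notation and not a badly specified dose. The section gives the percentage in words, names and cites the method, repeats 60% of reserve as the limit of progression and adds a Borg target of 12. These agree with one another; only the bracket does not. A physiotherapist who worked the printed line through for one patient would see a target above 220 − age and discard it. Sessions are supervised and monitored, and can be stopped for symptoms. The article mentions no session worksheet, so any effect on delivery is conjecture. With results expected in late 2025, a published correction may be all that is still possible.

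Most of this stands, and it limits the consequence: intent is recoverable, literal use is unlikely, and no outcome, allocation or analysis depends on the line. It does not make the line right. The Borg score is a parallel target and cannot supply the heart rate at which progression ends. The stopping examples are symptoms, with no heart-rate limit among them. Nor is this a detail that an article may leave to a fuller document, since the article prints the calculation and prints it wrongly. On timing, the Results section says: "Recruitment and data collection for the trial is ongoing". By the article's own account a check could still help.

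**Conclusion.** The concern holds. For every age, every positive resting rate and every intensity below 100%, the printed formula gives a value above 220 − age that falls as intensity rises. It therefore contradicts both the 40%-60% in its own sentence and the later instruction to raise speed to 60% of reserve. The excess over the stated target is (220 − age) × (1 − %), or 56 to 114 bpm over the four assumed patients in the table. Those figures measure how far the literal line is from the stated dose, not an error expected in delivery.

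That a bracket was misplaced is an inference, though moving it is enough to give the stated percentage. The safety and dose concern applies only if the printed line was used to set targets, which the article does not show. The sample size and the statistical analysis are unaffected. The line should be corrected.

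**What to change.** Replace the printed line with ((220 − age) − resting heart rate) × % intensity + resting heart rate, after the authors have checked it against the source they cite. Ask the trial team which calculation the treating physiotherapists have used to set targets; if it was the printed one, correct it at once and review the sessions already delivered.

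Two optional additions would help readers. One is a worked example, such as age 50 and resting rate 70 (assumed), giving 110 bpm at 40% and 130 bpm at 60%. The other is to report the share of reserve achieved, from the heart rates already recorded at each session.

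The cost is one corrected line and one query to the trial team. No new data are needed.

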### Statistical Design

The calculation to determine the sample size was carried out based on a previous randomized clinical trial that also compared the effect of aerobic training compared to usual care on the deleterious effects of chemotherapy in patients with breast cancer [11]. Our study was designed to detect a difference of 2.7 (SD 4) points in the physical fatigue score, in addition to a difference of 6.2 (SD 7) episodes of vomiting or nausea between the groups. A power of 80%, an α of 5%, and a loss to follow-up of 15% of the sample were considered. A sample of 94 patients (47 patients in each group) was estimated.

After the data collection, all analyses will be conducted following intention-to-treat principles and will be performed by a researcher who will not be involved in the study assessments and intervention.

For analyzing the effect of the intervention, after a descriptive analysis and the Shapiro-Wilk normality test with a visual analysis, the groups will be compared using a linear mixed model for fatigue, mobility, and chemotherapy-related symptoms before and after the intervention. The length of hospital stay will also be compared between groups using Kaplan-Meier survival analysis. The *χ*^2^ test will be used to compare the clinical complication rates between groups. Descriptive analysis will be used for recruitment, completion, and adherence rates and potential adverse events. The significance level will be set at 5%. For all these analyses, SPSS (version 21.0; IBM Corp) will be used.

For economic evaluation, the analysis will be performed using chemotherapy-related symptoms, fatigue, and mobility as outcomes, and the cost-utility analysis will use QALYs. Missing data will be handled using multiple imputation by chained equations. Ten complete data sets will be created (efficiency loss <5%). Pooled estimates will be calculated according to the Rubin rules [33]. Average cost differences between groups will be calculated for total and disaggregated costs. Incremental cost-effectiveness and cost-utility rates will be calculated by dividing the difference in total costs by the difference in effects. Uncertainty surrounding cost differences and incremental cost-effectiveness and cost-utility ratios will be estimated using corrected and accelerated bootstrap techniques (5000 replications). The latter will be presented graphically in cost-effectiveness plans [34]. Cost-effectiveness acceptability curves will be estimated to indicate the probability of interventions being cost-effective compared to each other at different willingness-to-pay values [35]. Sensitivity analyses will be performed to assess the robustness of the results. The first sensitivity analysis will be performed from a health care perspective, and the second sensitivity analysis will be performed per protocol. The economic evaluation will be carried out using Stata (version 14; StataCorp).

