### Assessments

First of all, a standardized printed form will be used that will include personal data (name, age, sex, place of birth, contact telephone number, education, monthly family income, marital status, and occupation) and anthropometric data (height and weight, measured as recommended by the National Institute of Health, Heart, Lung, and Blood) [19]; diagnosis of current illness; preexisting illnesses; current or past smoking history; history of alcohol consumption and medications used; previous chemotherapy or radiotherapy; whether the current chemotherapy is neoadjuvant, adjuvant, treatment of choice, or palliative; and whether the patient is or was a practitioner of physical activity and how often they performed such activity.

The primary outcome will be assessed via frequency and intensity. Discomfort caused by the main adverse symptoms of chemotherapy (such as pain, nausea, and dry mouth) will be assessed using the Memorial Symptom Assessment Scale, Brazilian version (MSAS-BR) [20]. This scale consists of 32 symptoms that are scored by the patient according to their frequency and intensity (1-4 points, with 1 being less intense and frequent) and the discomfort (0-4, zero being no discomfort) that this symptom caused the previous week. This scale gives us a final index, which consists of the average of the 3 domains (frequency, severity, and bother) and all items, in addition to 4 subscales: Psych, which assesses psychological symptoms (with six items); Phys H, which assesses the most prevalent physical symptoms (with 12 items); Phys L, which assesses the less prevalent physical symptoms (with 14 items); and the Global Distress Index, which measures 4 psychological and 6 physical symptoms [20,21]. This scale will be applied in the initial and final assessments by an evaluator blind to which group the patient belongs.

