Other outcomes will be assessed, such as fatigue, level of patient mobility, length of hospital stay, and clinical complications. Fatigue will be assessed using the Brief Fatigue Inventory, Brazilian version. This inventory consists of 9 items that are rated from 0 to 10 on a visual numeric scale. The first question is a dichotomous question about whether the patient has felt tired or fatigued in the last 7 days. Three items refer to the severity of fatigue at the time of assessment, the usual fatigue in the last 24 hours, and the worst fatigue in the last 24 hours, where 0 represents no fatigue and 10 “the worst fatigue imaginable.” The other 6 items refer to how fatigue interfered with different aspects of the patient’s life in the last 24 hours; these items are “general activities,” “mood,” “ability to walk,” “work” (including work outside and at home and daily tasks), “relationships with other people,” and “enjoying life,” where 0 means that it does not interfere and 10 means that it interferes completely [22,23]. This inventory will be applied in the initial and final assessments by an evaluator blind to which group the patient belongs.

The level of mobility will be assessed using the De Morton Mobility Index. This scale is made up of 15 activities, where 11 are classified as 0 or 1 (incapable or capable, respectively) and 4 are classified as 0, 1, or 2 (incapable, partial, and capable, respectively). Of the 15 activities, 3 are performed in bed, 3 in a chair, 4 involve static balance, 2 involve walking, and 3 involve dynamic balance. The scale was translated and validated in Brazilian Portuguese [24,25] and ranges from a score of 0, which represents low mobility, to 100, which represents high mobility. This index will be applied by an evaluator who is blind to which group the patient belongs and will be applied in the initial and final assessments.

In addition, the total number of days of hospital stay, possible clinical complications (cardiac, pulmonary, infectious, or neurological) arising from chemotherapy treatment, and the need for transfer to the intensive care unit will be accessed through the medical records of the patient.

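### The stated 80% power belongs to a physical-fatigue score and a vomiting/nausea count, not to the MSAS-BR primary outcome, for which no single score is designated

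*Protocol article*

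**What the plan says.** **Primary outcome (Protocol article, Assessments).** The paragraph opens with "The primary outcome will be assessed via frequency and intensity", and goes on to discomfort from the main adverse symptoms, measured with the MSAS-BR. Each of the 32 symptoms is graded 1 to 4 for frequency and intensity and 0 to 4 for discomfort. The same paragraph continues: "This scale gives us a final index, which consists of the average of the 3 domains (frequency, severity, and bother) and all items". It then lists four subscales: psychological, more prevalent physical, less prevalent physical, and the Global Distress Index.

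**Fatigue (Assessments).** The next paragraph begins "Other outcomes will be assessed, such as fatigue, level of patient mobility, length of hospital stay, and clinical complications". Fatigue is measured with the Brief Fatigue Inventory (BFI), described as severity items and interference items.

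**Sample size (Statistical Design).** "Our study was designed to detect a difference of 2.7 (SD 4) points in the physical fatigue score", together with "a difference of 6.2 (SD 7) episodes of vomiting or nausea between the groups". Both come from an earlier trial in breast cancer. "A power of 80%, an α of 5%, and a loss to follow-up of 15% of the sample were considered". The result: "A sample of 94 patients (47 patients in each group) was estimated". The section gives no MSAS-BR difference and no MSAS-BR standard deviation.

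**The concern.** A power statement tells the reader how likely the trial is to answer its primary question. Here it is attached to two other variables. The first is a fatigue score, and fatigue is not primary. The second is a count of episodes, which the MSAS-BR as described does not produce, because it grades frequency on a four-point scale. The BFI as described has no physical-fatigue score either. The power for the MSAS-BR is therefore unknown to anyone reading the protocol.

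The primary variable itself is also open. The opening sentence points to frequency and intensity, the final index averages three domains including discomfort, and four subscales follow. Unless one is designated before the arms are compared, the choice could later be questioned as made in the light of the results.

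Finally, the stated inputs do not obviously lead to 94, so the calculation cannot be followed.

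**Working it through.** **Inputs (Statistical Design).** Fatigue: difference 2.7, SD 4, so d = 2.7/4 = 0.675. Vomiting or nausea: difference 6.2, SD 7, so d = 6.2/7 = 0.886. Power 80%, α 5%, loss 15%, 1:1 allocation (Design). Sidedness and test are not stated; I assume a two-sided comparison of two means.

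**1. Trying to reproduce 94.** Per arm, n = 2(z₀.₉₇₅ + z₀.₈₀)²/d² = 2 × 7.849/d².

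| Sizing variable | n per arm, normal | n per arm, t-test | After dividing by 0.85 | Total |
|---|---|---|---|---|
| Fatigue, d = 0.675 | 34.5, so 35 | 35.4, so 36 | 41.2 or 42.4, so 42 or 43 | 84 or 86 |
| Vomiting/nausea, d = 0.886 | 20.01, so 21 | 21.02, so 22 | 24.7 or 25.9, so 25 or 26 | 50 or 52 |

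Other readings of the same inputs also miss 94:
- Inflating by 1.15 instead of dividing by 0.85: fatigue total 82 or 84.
- One-sided 5%: 66.
- α split to 2.5% for two variables: 100 or 104.
- 80% joint power on both variables, taken as independent: 38 per arm, total 90.

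Two unstated assumptions do reach 47 per arm:
- A rank test with relative efficiency 0.864: 34.45/0.864/0.85 = 46.9, so 47.
- 85% power in place of 80%, normal approximation: 39.4/0.85 = 46.4, so 47.

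Both depend on rounding only at the end. Rounding at each step gives 50 per arm for the rank test (from the t-based n) and 48 for 85% power.

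**2. What 94 gives on the stated inputs.** 47 × 0.85 = 39.95, about 40 evaluable per arm. The t-test power is then 84.6% for the fatigue difference and about 97% for vomiting/nausea, ignoring clustering.

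**3. What 94 gives for the primary outcome.** Without an MSAS-BR difference and SD, power can be given only for assumed effects. At 40 per arm, t-test, two-sided 5%, no clustering, it is about 60% for d = 0.5 and 42% for d = 0.4. The smallest d detectable at 80% power is about 0.63.

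The Randomization section allocates rooms of 2 to 4 beds. It gives no intracluster correlation and no number of patients covered by each room assignment. The design effects below are therefore assumptions. The detectable d is that of a t-test with 40/(design effect) patients per arm:

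| Assumed design effect | Detectable d at 80% power |
|---|---|
| 1.0 | 0.63 |
| 1.1 | 0.67 |
| 1.2 | 0.70 |
| 1.4 | 0.75 |
| 1.8 | 0.86 |

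**The case against.** **The sizing variables are not foreign to the trial.** The Objective and Introduction define chemotherapy-related symptoms as nausea, vomiting, asthenia and weakness, the MSAS-BR covers symptoms, and fatigue is a listed outcome with its own model. This stands: the constructs are measured. What fails is the metric, and fatigue is not primary. A difference of 6.2 episodes cannot be converted to a graded score without further data.

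**A single score does exist.** The MSAS-BR has a final index, and the subscales may be mentioned only to describe the instrument. This also stands. A reader might infer that the primary outcome cannot be one score, but the text does not support that. The fault is that no score is designated.

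**94 may be undocumented rather than wrong, and it is larger than needed.** A rank-test efficiency or 85% power would explain it, and the surplus is 94 − 86 = 8 to 94 − 84 = 10 patients. This stands too. A reader might infer a miscalculation that leaves the trial too small for its stated differences; ignoring clustering, the figures show the reverse. Nor can the surplus be read as an allowance for room randomisation, since only power, α and loss are listed.

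**Multiplicity.** A reader might treat the index and four subscales as five independent tests and compute an inflated error rate. The documents do not support that: nothing says all five will be tested as primary, the index contains the subscale items, and multiplicity may be handled in an analysis plan that is not shown.

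**Conclusion.** The point holds. The 80% power in Statistical Design is not power for the primary outcome named in Assessments, and no MSAS-BR score is designated as primary. These are the parts that need correcting, because they concern what the trial is able to answer.

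The arithmetic is secondary, a fault of traceability. Under a two-sided t-test the inputs give 84 to 86 (fatigue) or 50 to 52 (vomiting/nausea), and 94 gives about 85% power for the fatigue difference if clustering is ignored.

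For the MSAS-BR, about 80 evaluable patients detect d of about 0.63 at best, rising to 0.86 at an assumed design effect of 1.8. This does not show that the trial is underpowered for its primary outcome. The documents give no MSAS-BR effect or SD against which to judge it, so the power is unknown. The figures rest on two-sided 5%, 15% loss and a comparison of final scores. The planned mixed model uses baseline values and might recover some precision, but no baseline-to-final correlation is given from which to credit it.

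**What to change.** By amendment, before any comparison by arm (the Results section says recruitment and data collection are ongoing):

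1. Designate one MSAS-BR score at the final assessment as the sole primary endpoint, tested at two-sided 5%. The final index over all items is the natural choice. The sponsor must confirm that frequency and intensity was not meant as a narrower score. Make the subscales, the BFI and the De Morton Mobility Index secondary.
2. Replace the power statement with what 94 randomised (about 80 evaluable) can detect on that score: about 0.63 standard deviations at 80% power ignoring room clustering, with the range over design effects shown above and labelled as assumed. Convert it to MSAS-BR points with the baseline SD pooled over both arms, obtained blind to arm.
3. State the test and assumptions that led to 94, or correct the derivation.

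Enrolment stays at 94 and no unblinding is needed. The cost is a substantive protocol amendment, since it fixes the primary variable and uses accrued baseline data, and a stated detectable effect that looks less favourable than the present text.
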